### Interventions

The participants from both groups will receive a group exercise programme, including a combination of general, stabilisation, strengthening and resistance exercises. The group exercise programme will be led by a physiotherapist with at least 2 years’ clinical experience and consists of a 45-min group session with up to 10 people, delivered twice a week for 3 months. See Table 1 for details of the intervention which accords to the Description of the intervention using the Template for Intervention Description and Replication (TIDieR) Checklist.

**Table 1 Tab1:** Description of the intervention using the Template for Intervention Description and Replication (TIDieR) Checklist

1. Brief name	The Physical Activity for Back Pain (PAyBack) trial
2. Why?	Low back pain (LBP) is one of the most disabling conditions imposing an enormous economic burden to society and individuals. Although physical activity and exercise are effective in reducing pain and disability in patients with chronic LBP, these improvements are at best moderate and not sustained over the long term. Furthermore, physical activity-based interventions are not effective for increasing physical activity levels of patients with chronic musculoskeletal pain. We would argue that current interventions are not designed to change patients’ behaviour toward an active lifestyle
3. What materials?	Participants allocated to the intervention group will receive the activity monitor *Fitbit Flex*. For the purpose of the current study, we will blind participants to the feedback lights by covering all wristbands with heat-shrink tubing. Participants allocated to the control group will receive a *Fitbit Flex* wristband without the accelerometer containing a material that mimics the weight of the accelerometer and the heat shrink tubing to cover the wristband as in the intervention group
4. What procedures?	The participants from both groups will receive a group-based exercise programme, including a combination of general, stabilisation, aerobic, strengthening and resistance exercises: *Multimodal physical activity intervention group* - Health coaching sessions to identify facilitators and barriers to physical activity participation and to assist participants to achieve their physical activity goals by providing ongoing education and support. An individualised and realistic physical activity plan will be developed for each participant, considering the presence of potential cardiovascular risk factors and participants’ current activity level. In addition, during the health coaching sessions, the physiotherapist will educate patients on the benefits of staying active and will help them to recognise and control, if relevant, pain-related fear, catastrophising and negative thoughts and emotions about pain - *Fitbit Flex* to give feedback on the amount of daily physical activity achieved, used by the participants as a motivational tool and to provide feedback during the health coaching sessions *Control group* - Sham coaching giving participants the opportunity to talk about their LBP or other problems, but without providing any therapeutic advice - Sham *Fitbit* providing the same information given to the intervention group
5. Who provided?	A physiotherapist who attended a health coaching course, obtained practice experience from experienced health coaches and trained to use active listening techniques
6. How?	Supervised exercises will be delivered in group exercises sessions. The health coaching and sham coaching sessions will be delivered on an individual basis via face-to-face and telephone contact
7. Where?	The trial will be conducted at two outpatient physiotherapy clinics in Presidente Prudente, Sao Paulo, Brazil.
8. When and how much?	The group exercise programme will be led by a physiotherapist with at least 2 years’ clinical experience and will consist of 45-min group sessions with up to 10 people, twice a week for 3 months For health coaching, a total of 12 health coaching sessions, each session lasting for 30–60 min, will be provided over a 3-month period. The intervention will be delivered during one face-to-face visit each week for the first 6 weeks and then during one telephone contact each week for the last 6 weeks. The participants will be encouraged to wear the *Fitbit* during all waking hours for the 3-month intervention period For the control group, the sham health coaching will consist of one weekly session (first 6 weeks being a face-to-face session and the last 6 weeks by telephone contact), each session lasting for 30–60 min, over a 3-month period. In addition, the participants will receive the sham *Fitbit* and be encouraged to wear it during waking hours for the 3-month study period
9. Tailoring	For the intervention group, the individualised activity plan will be delivered considering the presence of potential cardiovascular risk factors and participants’ current activity level. In addition, the physical activity goals will focus on attempting to meet the physical activity recommendations of at least 150 min of moderate-intensity or 75 min of vigorous-intensity physical activity throughout the week or walking between 7000 to 10,000 steps per day

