## Methods

### Design

This study will be a parallel randomised controlled trial (RCT) conducted at two outpatient physical therapy clinics in Presidente Prudente, Brazil. This protocol conforms to the Consolidated Standard of Reporting Trials (CONSORT) Statement and is registered at ClinicalTrials.gov (NCT03200509). Figure 1 shows the study design. The Standard Protocol Items: Recommendations for Intervention Trials (SPIRIT) Checklist is provided in Additional file 1 and the SPIRIT Diagram is included in the Fig. 2.

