### Sample size

A sample size calculation was performed based on an objective measure of physical activity level, i.e. counts per min, derived from an accelerometer. A total of 160 participants (80 patients per group) will be required to detect a 20% between-group difference in physical activity levels (mean difference between groups of 59.2 counts per min, a standard deviation of 111.6 counts per min) with a power of 0.80, alpha of 0.05 accounting for a 15% loss to follow-up. The counts per min parameters used in the sample size calculation are from a previous study conducted with a similar population [22]. The total of 160 participants is enough to detect a between-group difference of 1 point (standard deviation (SD) = 1.84) in the numerical pain rating scale and of 4 points (SD = 4.9) in the Roland Morris Disability Questionnaire (RMDQ) with a power of 80%, an alpha of 0.05 and 15% dropout as reported in a previous trial with this population [23].

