### Data analysis

Continuous variables will be reported using mean (standard deviation) or median (interquartile range), depending on the data distribution, and dichotomous and categorical variables will be reported using frequencies (proportion). All data will be analysed following intention-to-treat principles. The difference between groups will be analysed with linear mixed models using fixed effects for group, time and group-versus-time interaction and random intercepts for individuals to account for the dependence of repeated measures. Statistical significance will be set at 0.05. We will report the number of participants with missing scores for each outcome. The statistical software SPSS V.20.0 (IBM corporation, Somers, NY, USA) will be used for data analysis. Planned subgroup analyses will investigate differences in effects of the intervention by physical activity levels at baseline assessment and pain self-efficacy. In addition, we will also conduct secondary analyses to investigate the treatment effects considering the adherence to treatment using a complier average causal effect (CACE) approach.

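### Exercise classes of up to 10 are a level of the design that the stated mixed model omits; if classes are arm-specific, which the protocol does not say, standard errors for all three primary outcomes are too small

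*Protocol article*

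**What the plan says.** - **Delivery.** The Interventions section and Table 1 give both arms the same physiotherapist-led programme, each class a "45-min group session with up to 10 people", twice weekly for 3 months. The Design section says the trial is "conducted at two outpatient physical therapy clinics in Presidente Prudente, Brazil".
- **What differs between arms.** Coaching or sham coaching is given individually (Table 1), together with a real or sham monitor. Participants are randomised as individuals (Procedures).
- **Model.** The Data analysis section names fixed effects for group, time and their interaction, with "random intercepts for individuals to account for the dependence of repeated measures". It has no term for class.
- **Sample size.** The target is 80 per arm. For counts per min it rests on a difference of 59.2 and an SD of 111.6, and it is set "with a power of 0.80, alpha of 0.05 accounting for a 15% loss to follow-up". The section adds pain (difference 1, SD 1.84) and the Roland Morris questionnaire (RMDQ; difference 4, SD 4.9). It uses no ICC or design effect.
- **Not stated.** Whether classes are arm-specific or mixed, and whether they are closed groups or take new members as others leave.

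**The concern.** People who share an instructor, a time slot and classmates for 3 months may have correlated outcomes at the end. The only dependence the stated model handles is that between repeated measures on one person.

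If each class holds one arm only, class effects do not cancel between arms. They add to the variance of the treatment contrast, and the model does not count them. Intervals for counts per min, pain and RMDQ are then too narrow and the tests reject too often. If classes mix the arms, class effects largely cancel from the contrast but remain in the residual, so intervals are slightly too wide. The first case affects the validity of all three primary comparisons. The second costs a little precision.

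**Working it through.** **Inputs from Sample size.** 80 per arm; 15% loss, so 80 × 0.85 = 68 analysed per arm; alpha 0.05, taken as two-sided because sidedness is not stated; differences and SDs as above. **From Interventions:** at most 10 per class; a full class less 15% leaves 8.5. **Assumed:** class ICC 0.01 to 0.05.

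**1. The plan's own figure.** For counts per min, d = 59.2/111.6 = 0.530.

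n per arm = 2(1.960 + 0.842)²/d² = 55.8, so 56. Then 56/0.85 = 65.9, so 66 per arm and 132 in total.

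The stated inputs therefore need 132, not 160.

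**2. Power at 68 per arm under independence.** Power = Φ(d√(68/2) − 1.960).

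- Counts per min: Φ(3.093 − 1.960) = 0.871
- Pain (d = 0.543): Φ(3.169 − 1.960) = 0.887
- RMDQ (d = 0.816): Φ(4.760 − 1.960) = 0.997

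**3. Arm-specific classes, clustering ignored.** Design effect DE = 1 + (m − 1) × ICC. True error = 2[1 − Φ(1.960/√DE)]. Shortfall in the standard error = 1 − 1/√DE. Power for counts per min allowing for clustering = Φ(3.093/√DE − 1.960).

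| m | ICC | DE | True error | SE too small by | Power, counts per min |
|---|---|---|---|---|---|
| 8.5 | 0.01 | 1.075 | 0.059 | 4% | 0.847 |
| 8.5 | 0.05 | 1.375 | 0.095 | 15% | 0.751 |
| 10 | 0.01 | 1.09 | 0.061 | 4% | 0.842 |
| 10 | 0.02 | 1.18 | 0.071 | 8% | 0.813 |
| 10 | 0.05 | 1.45 | 0.104 | 17% | 0.729 |

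A simulation of a two-sample t-test that ignores class (20,000 runs, 16 classes of 10, 15% loss) gave error rates of 0.066 at ICC 0.02 and 0.094 at ICC 0.05, in line with the m = 8.5 formula.

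**4. ICC at which power reaches 80%.** The largest tolerable DE is (d√34/2.802)², and the break-even ICC is (DE − 1)/(m − 1).

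- Counts per min: DE 1.219; ICC 0.024 at m = 10, 0.029 at m = 8.5, 0.055 at m = 5
- Pain: DE 1.279; ICC 0.031 at m = 10, 0.037 at m = 8.5
- RMDQ: DE 2.887; ICC 0.21 at m = 10. At ICC 0.05 and m = 10, power is Φ(4.760/√1.45 − 1.960) = 0.977

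**5. Mixed classes, balanced between arms.** DE = 1 − ICC. At ICC 0.05 the true error is 0.044 and intervals are 1/√0.95 = 1.026 times as wide as they need be. At ICC 0.01 the error is 0.049. Power with class modelled is 0.888 at ICC 0.05, against 0.871 with no clustering.

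All of this concerns a single comparison at 3 months. It ignores any gain from baseline or repeated measures and uses normal quantiles.

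**The case against.** **The harm rests on an unstated fact.** Both arms follow the same class programme, the components under test are delivered individually, and randomisation is individual. A reader might infer arm-specific classes from the sham procedure: control participants hand in a sham monitor before class and are told that the physiotherapist cannot see their data, and mixing arms could expose the difference. That makes separation plausible, but the protocol does not say it. This objection stands, so the inflated error is a conditional finding.

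**Power.** A reader might infer that omitting clustering means the 80% is overstated, or that all three primary tests could fall below it. The figures do not support either reading. The stated inputs give 87% with 68 per arm, a margin equal to a design effect of 1.22, and RMDQ stays at 97% or more up to ICC 0.05. This objection also stands, with one limit: the thresholds use large-sample quantiles. With only 16 full classes, the pessimistic bound of 14 between-class degrees of freedom gives 0.754 at ICC 0.02 and m = 10, and 0.820 even at ICC 0.

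**Class size.** Ten is a ceiling before loss, so m = 10 with 68 analysed per arm is an upper bound. Smaller classes shrink the effect: at m = 5 and ICC 0.05 the true error is 0.074.

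**Scope.** A class term might be left to a statistical analysis plan that is not shown. However, the article commits to a specific random-effects structure, and that structure omits a level which the same article describes. Spare power does not answer this, because it does not correct an error rate or interval coverage.

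**Conclusion.** The stated model omits class as a source of dependence. With arm-specific classes, an assumed ICC of 0.01 to 0.05 and 8.5 to 10 analysed per class, standard errors for all three primary outcomes are about 4% to 17% too small and the true type I error is about 0.06 to 0.10. With mixed classes the test is slightly conservative (0.044 to 0.049) and no power is lost. The protocol does not say which case applies.

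The stated 80% power is not shown to be overstated. On the normal approximation, counts per min falls below 80% only with arm-specific classes and an ICC above about 0.024 (10 per class) to 0.029 (8.5 per class). The ICC is an assumption throughout. The point is worth acting on because the remedy is cheap and the adverse case touches every primary comparison.

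**What to change.** 1. State whether classes are arm-specific or mixed.
2. Record the class to which each participant is first assigned, defined by clinic, time slot and intake period. Recruitment runs from August 2017 to December 2018 and the programme lasts 3 months, so clinic and slot alone could merge several successive groups.
3. Add to the mixed model for the three primary outcomes a random class effect that acts on post-baseline visits (class-by-time), with Satterthwaite degrees of freedom. A class intercept that is constant over time is not enough: it adds the same amount at baseline and at follow-up, cancels from the group-by-time contrast, and leaves its standard error uncorrected.
4. Report the estimated class ICC for each primary outcome.
5. Note in the sample-size paragraph that the power figure assumes no class clustering. The gap between 160 and the 132 that its inputs give can be explained in the same place.

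A fixed clinic effect is optional. If it is added, the model no longer reduces to the planned one when the class variance is estimated as zero.

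The cost is one recorded variable, one extra variance component, a few lines of text, and somewhat wider intervals if classes are arm-specific. No extra participants are needed.

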#### Multimodal physical activity intervention group

Participants randomised to the intervention group will receive, in addition to the exercise programme, a health coaching programme together with an activity monitor. The health coaching will be provided by a physiotherapist who has attended a health coaching course (http://www.wellnesscoachingaustralia.com.au) and has been mentored by experienced health coaches participating in ongoing trials [24, 25]. The purpose of the health coaching is to identify facilitators and barriers to physical activity participation and to assist participants to achieve their physical activity goals by providing ongoing education and support. The physical activity goals will focus on reducing time spent in sedentary activities as well as attempting to meet the physical activity recommendations of at least 150 min of moderate-intensity or 75 min of vigorous-intensity physical activity throughout the week [26] or walking between 7000 to 10,000 steps to per day [27, 28]. An individualised and realistic physical activity plan will be developed during the first health coaching session between the physiotherapist and the participant considering the presence of potential cardiovascular risk factors and participants’ current physical activity. During the health coaching session, the physiotherapist will educate patients on the benefits of staying active and will help them to recognise and control, if relevant, pain-related fear, catastrophising and negative thoughts and emotions about pain [29]. A total of 12 health coaching sessions, each session lasting for 30–60 min, will be provided over a 3-month period. The intervention will be delivered during one face-to-face visit each week for the first 6 weeks and then during one telephone contact each week for the last 6 weeks.

The activity monitor, *Fitbit Flex* (*Fitbit* Inc., San Francisco, CA, USA), will be given to all participants in the intervention group. The *Fitbit Flex* is a small (140–176 mm) three-axis accelerometer inserted in a wristband designed to give feedback on the amount of daily physical activity achieved. Participants will be encouraged to wear the activity monitor during waking hours. The *Fitbit Flex* has five indicator lights that flash various patterns depending on what the tracker is doing. For the purpose of the current study, we will blind the participants to the lights by covering all wristbands with heat-shrink tubing (Fig. 3). The activity monitor data will be uploaded while the participants are attending the group exercise classes and the physiotherapist will use these data to provide feedback on the amount of physical activity during the health coaching sessions. The activity monitors will be charged while the physical activity data are being uploaded.

**Fig. 3 Fig3:**
[figure not shown]
The *Fitbit Flex*. **a** the original *Fitbit Flex*. **b** the *Fitbit Flex* with heat-shrink tubing covering the indicator lights

#### Control group

The participants allocated to the control group will receive, in addition to the exercise programme, sham health coaching and a sham activity monitor. Sham health coaching will consist of one weekly session (the first 6 weeks will be a face-to-face session and the last 6 weeks will be telephone contacts), each session lasting for 30–60 min, over a 3-month period, based on a ‘reflective, non-directive approach’ described previously elsewhere [30]. The physiotherapist will be trained to use active listening techniques, giving participants the opportunity to talk about their LBP or other problems. In response, the treating physiotherapist will reply in a warm and empathic manner, with a special interest in the report, but without providing any therapeutic advice. This strategy is designed to control for time with a physiotherapist and the therapeutic alliance that occurs within a consultation. A previous study found that this approach is credible which maximises participant blinding [30].

All participants in the control group will be given a sham activity monitor, which will consist of a *Fitbit Flex* wristband without the accelerometer. A material that mimics the weight of the accelerometer will be inserted in the wristband and heat-shrink tubing will be used to cover the wristband as in the intervention group. The same information given to the intervention group about the activity monitor will be provided to the participants in the control group. Nevertheless, the participants will be informed that the treating physiotherapist does not have access to the *Fitbit* data for the control group. Participants in the control group will give their sham *Fitbit* to the physiotherapist before each exercises class and will be told that this procedure is needed to charge the *Fitbit*.

### Outcomes

The measures will be collected using REDCap (Research Electronic Data Capture) [31] hosted at Sao Paulo State University. Data will be collected and stored in spreadsheets by assessors blinded to group allocation. At baseline assessment, the physiotherapist assessors will collect data on participant characteristics (i.e. age, gender, educational level, presence of comorbidities, medication use and employment status). To characterise the study participants, information on fear of movement measured with the Tampa Scale for Kinesiophobia (TSK) [32] and prognosis risk measured with the Örebro Musculoskeletal Pain Screening Questionnaire (ÖMPSQ) [33] will be collected at baseline. Outcome measures will be assessed at baseline, post intervention (i.e. 3 months after randomisation) and at 6 and 12-month follow-ups. Details on the primary and secondary outcomes are reported below:

#### Primary outcomes

Physical activity – counts per min is the main objective measure of physical activity and will be measured with the Actigraph GT3X (ActiGraph, LLC, Pensacola, FL, USA). The Actigraph GT3X is a non-invasive, small (4.6 × 3.3 × 1.5 cm) triaxial accelerometer worn above the right hip for seven consecutive days during waking hours. Acceleration data will be sampled at 30 Hz and analysed at 60-s epochs. A complete data set for each patient will be defined as having at least 10 h/day of monitored wear over at least 5 days [34]. Non-wear periods will be defined as time intervals of at least 60 consecutives min of zero counts, with an activity interruption allowance of 0 to 100 counts/min lasting a maximum of two consecutive days [35]. These parameters have been used in previous studies from our group [22, 36]. Counts per min will be calculated by dividing the sum of activity counts of the vertical axis by the number of valid daysDisability – the Roland Morris Disability Questionnaire (RMDQ) [37] will be used to measure disability. The RMDQ consists of 24 yes-or-no questions with total scores ranging from 0 to 24 and higher scores indicating greater disabilityPain intensity – Numerical Rating Scale for pain assessment (NRS) will be used to measure pain intensity. The NRS evaluates the pain intensity in the last week through an 11-point-scale from 0 to 10 with higher scores indicating greater pain intensities

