#### Secondary outcomes

Other objective measures of physical activity, such as time spent in light and moderate-vigorous physical activity, number of steps and time spent in sedentary behaviour, will be considered secondary outcomes. These data will be collected with the same procedure reported for counts per min. Sedentary time will be defined as values less than 100 count/min, light physical activity will be defined as values between 100 and 2019 counts/min and moderate-vigorous physical activity will be defined as values greater than 2020 counts/min [34]Self-reported physical activity level will be measured with the Baecke Habitual Physical Activity Questionnaire [22]. This questionnaire consists of 16 items covering three dimensions: leisure-time and locomotive physical activities; leisure-time physical exercises; and occupational physical activities. The total score ranges from 3 to 15, with higher scores indicating higher physical activity levelsSelf-reported sedentary behaviour will be measured with questions about the time spent in sedentary behaviour across five different domains in a usual weekday [38]: workplace, commuting, school/university, watching TV, and computer use. Before quantifying the time spent in each sedentary activity, the participants will be asked if they are exposed, or not, to each behaviour. We will use the sum of the domains as well as the time spent in each sedentary behaviourDepression will be assessed with The Center for Epidemiological Studies – Depression (CES-D) scale [39]. The CES-D scale assesses the frequency of depression symptoms in the last week with 20 questions. Total scores range from 0 to 60 and higher scores indicate higher depression levelsQuality of life will be assessed using the EuroQol Visual Analogue Scale (EQ-VAS) [40]. In the EQ-VAS, respondents report their perceived health status with a grade ranging from 0 (the worst possible health status) to 100 (the best health status)The Pain Self-Efficacy Questionnaire (PSEQ) [41] will be used to assess pain self-efficacy. The PSEQ contains 10 items with scores ranging from 0 to 6. Final scores range from 0 to 60 with higher scores indicating more confidence to perform an activity despite the painWeight-related outcomes – Body Mass Index and waist-to-hip circumference will be used to measure weight-related outcomes. Body Mass Index will be calculated based on weight and height measured by a digital scale and an stadiometer and waist and hip circumference using an anthropometric measuring tape. Waist circumference will be measured midway between the 10th rib and the top of the iliac crest and hip circumference as the widest part over the buttocks to the nearest 0.5 cm

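### The accelerometer non-wear rule sets its interruption limit in days, so as written it has no effective limit and could score prolonged worn sitting as non-wear

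*Protocol article*

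**What the plan says.** All of this is in the protocol article, Methods, Outcomes. Under Primary outcomes, the ActiGraph is "worn above the right hip for seven consecutive days during waking hours". The resolution is given as "Acceleration data will be sampled at 30 Hz and analysed at 60-s epochs". The non-wear rule has two parts: "Non-wear periods will be defined as time intervals of at least 60 consecutives min of zero counts", and then "with an activity interruption allowance of 0 to 100 counts/min lasting a maximum of two consecutive days". A record counts as complete under this rule: "A complete data set for each patient will be defined as having at least 10 h/day of monitored wear over at least 5 days". The article gives a citation for the non-wear rule and says the parameters were used in the group's earlier studies. The same paragraph obtains counts per min by dividing summed vertical-axis counts by the number of valid days.

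Under Secondary outcomes, "Sedentary time will be defined as values less than 100 count/min". For the other accelerometer measures, sedentary time among them, the article says: "These data will be collected with the same procedure reported for counts per min".

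**The concern.** Every other element of the rule is on a scale of minutes or hours: 60-s epochs, a 60-min window, a 10 h valid day. A tolerance of two days inside a 60-min window does not belong to that scheme. The tolerated band, 0 to 100 counts/min, is also almost exactly the article's definition of sedentary behaviour. With no working limit on how long the interruption may last, the rule cannot separate a device that has been taken off from a participant who sits still for a long time.

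The rule decides which minutes and days enter counts per min, a primary outcome and the one the sample size rests on. It also decides how much sedentary time is recorded. Errors would fall mainly on the least active participants, whose days contain the longest sitting stretches.

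**Working it through.** No figure in the article depends on this rule, so there is nothing to reproduce. The check sets the parts of the rule side by side and then sizes the effect under stated assumptions.

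**1. Does the limit ever take effect?** Two days × 24 h × 60 = 2,880 one-minute epochs. A waking-hours day is far shorter; the assumed 14 h day is 840 epochs. Within a recording day the limit cannot be reached.

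**2. What is exposed?** The allowance is 0–100 counts/min and the sedentary band is below 100 counts/min. A stretch is exposed if it lasts at least 60 min, begins and ends on zero counts, and has no minute above 100. Shorter sitting, or sitting broken by any minute above 100, is not affected.

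**3. Simple arithmetic.** The Sample size section gives a difference of 59.2 counts/min as 20%, so the implied mean is 59.2 / 0.20 = 296 counts/min. Assumed: 840 min of true wear, and sedentary minutes averaging 10 counts/min. Total counts = 296 × 840 = 248,640.

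| Worn sitting removed | Counts per wear minute | Change in a retained day's total |
|---|---|---|
| 60 min | (248,640 − 600) / 780 = 318.0 (+7%) | −600 / 248,640 = −0.2% |
| 120 min | (248,640 − 1,200) / 720 = 343.7 (+16%) | −0.5% |
| 180 min | (248,640 − 1,800) / 660 = 374.0 (+26%) | −0.7% |

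With the sedentary mean varied from 0 to 50 counts/min, removing 1 to 4 h raises counts per wear minute by about 6% to 40% and changes a retained day's total by 0% to −4.8%. Removing more than 840 − 600 = 240 min puts the day below 10 h.

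**4. Which divisor applies?** The outcome's name and the 296 scale imply wear minutes; a daily total at that level would be about 248,640. The text states valid days. Only the middle column shows direct inflation, and it needs the divisor that the text does not state.

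**5. Simulation.** 400 days of 840 min per setting. Assumed: ordinary sedentary bouts averaging about 20 min, active bouts averaging about 8 min, sedentary minutes zero with probability 0.6 and otherwise 1–99 counts, plus 0, 1, 2 or 4 added 90-min sitting bouts per day. All days are fully worn, so true wear is 840 min.

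| Added bouts | Wear scored, two-minute limit | Days valid | Wear scored, two-day limit | Days valid |
|---|---|---|---|---|
| 0 | 831 min | 100% | 738 min | 93.5% |
| 1 | 818 min | 100% | 642 min | 72.5% |
| 2 | 800 min | 100% | 549 min | 25.5% |
| 4 | 770 min | 99% | 374 min | 0% |

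For 0, 1 and 2 added bouts, counts per wear minute were 307, 275 and 245 with no allowance, and 347, 355 and 367 under the two-day limit. Counts per valid day rose by about 1%, 3% and 8% (258,069 to 260,591; 230,550 to 237,745; 205,975 to 221,470), only because the more sedentary days dropped out.

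**The case against.** The strongest reply is that this is a slip of one word in a short description of an established rule. The article cites a source and earlier use by the group, and nothing in it shows that data are being scored with a two-day tolerance. That stands as a statement about likelihood. It does not make the published rule correct, and the article does not state the intended limit anywhere else.

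A second reply concerns the reading. If an uninterrupted hour of zeros must come first, and the allowance only bridges interruptions to it, much less worn sitting would qualify. That is fair. The wording allows either reading, so the simulated losses apply to the broader one.

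A reader might infer three stronger things that the document does not support:

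- **That ordinary sitting in general is deleted.** Only unbroken stretches of 60 min or more at or below 100 counts/min are exposed.
- **That the primary outcome is inflated by 7%, 16% or 26%.** Those figures need a wear-minute divisor. With the stated valid-day divisor, a retained day's total falls slightly. That divisor is a separate problem in the same paragraph and needs its own correction.
- **That the distortion can be compared with the 59.2 counts/min target, or is shown to pull the effect towards zero.** A shift in level within a person is not a between-group difference, and a shift common to both arms cancels. Coaching aims partly to reduce sedentary time, so a differential shift is possible, but nothing available sizes it.

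**Conclusion.** The point holds as a defect in the stated scoring rule. The two-day limit does not fit the epochs, window, wear schedule and valid-day rule around it, and it leaves interruptions effectively unlimited. It is probably a unit slip.

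If the rule were followed as written, two consequences would arise whichever divisor is used: sedentary time would be understated, and days of inactive participants would be lost selectively under the 10 h on 5 days criterion. Direct inflation of counts per min is conditional on a wear-minute divisor; under the stated divisor, any rise comes only from losing sedentary days (about 1% to 8% in the simulation).

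All sizes rest on the assumed 14 h day, the assumed sitting patterns, the broader reading of the rule and literal application. They illustrate direction and are not estimates for this trial. The intended unit is a strong inference from the rule itself, but the cited source is not at hand to confirm it.

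**What to change.** State the interruption limit in minutes. The rule's own units suggest two consecutive minutes; confirm this against the cited algorithm and the settings in the group's earlier studies before publishing the correction. State also whether an uninterrupted run of zeros is required before the allowance applies. Check that the scoring software uses the confirmed setting, and re-score any recordings already processed under a day-scale limit. The cost is one word or a short clause, a check of the settings and, at most, re-running the scoring on stored files. No new data are needed.
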